### Adverse events

The number of cases and proportion of adverse events in the active and sham stimulation groups will be calculated during the acute treatment period and in the subsequent observation period, respectively. Both groups will be compared and analyzed using chi-square test or Fisher test.

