## Introduction

Bipolar depression is a mood disorder consisting of depressive, manic, and hypomanic episodes. It has a high recurrence rate, rapidly advances to more severe episodes, severe disability, and frequently takes a chronic course (1, 2). Patients with bipolar depression also have a high risk of suicide attempt and a manic switch (3). Patients spend most of the time in a depressive state. According to the treatment guidelines developed by the Japanese Society of Mood Disorders, depressive episodes of bipolar depression (4) are treated with mood stabilizers or atypical antipsychotics, specifically quetiapine (300 mg/day), lithium (0.8 mEq/L of blood concentration), olanzapine (5–20 mg/day), lurasidone (20–60 mg/day), or lamotrigine (200 mg/day). However, in clinical practice, patients often show no response to pharmacotherapy, which results in prolongation of the depressive episode and difficulty in achieving remission. Other recommended treatments by the Japanese Society of Mood Disorders include the combined use of lithium (0.6–0.8 mEq/L of blood concentration) and lamotrigine (200 mg/day), therapeutic dose of lithium or valproic acid and lamotrigine, or electroconvulsive therapy (4). ECT requires pretreatment with intravenous anesthetics and muscle relaxants and may cause temporary memory impairment, including amnesia. Thus, it is necessary to develop therapeutic methods to treat intractable bipolar disorder given the limited number of treatment options. Transcranial magnetic stimulation (TMS) is a non-invasive technique that stimulates the brain through the generation of an eddy current, which appears in association with a variable magnetic field forming around a coil supplied with an electrical current. Delivery of the TMS pulses in short intervals is referred to as repetitive TMS (rTMS). High-frequency stimulation affects cortical excitability in a facilitatory manner (5), whereas low-frequency stimulation suppresses cortical excitability (6). In Japan, rTMS has been approved by the Ministry of Health, Labor, and Welfare as an insurance-covered therapeutic method for the treatment of refractory major depressive disorder. Many clinical studies used rTMS to treat refractory depression, but only a few studied bipolar disorders. To address this issue, Zengin et al. (7) showed that rTMS treatment to the left prefrontal cortex is effective and safe for 29 participants with treatment-resistant bipolar depression by randomized controlled trial. McGirr et al. (8) showed a double-blind, 4-week, randomized clinical trial for 37 participants of intermittent theta burst stimulation (iTBS) to the left dorsolateral prefrontal cortex (DLPFC). The iTBS to the left DLPFC was not efficacious in the treatment of bipolar depression. A systematic meta-analysis of randomized double-blinded comparative studies on depression, bipolar disorder, or both was performed to assess the treatment efficacy for bipolar disorder. A total of 19 clinical studies that met the quality criteria were included, involving 181 patients with bipolar disorder (9). This meta-analysis showed that the response rate for patients receiving active stimulation was 44.3%, whereas it was 25.3% for sham stimulation, suggesting that the treatment was effective in those receiving active stimulation for bipolar depression (9). The therapeutic efficacy was compared based on the number needed to treat (NNT); the NNT in the active stimulation group was 6 (95% confidence interval [CI], 4–15) compared to the control sham stimulation group. The NNT for high-frequency stimulation to the left prefrontal cortex was 7 (95% CI, 4–112), whereas that for low-frequency stimulation to the right prefrontal cortex was 3 (95% CI, 2–6) (9), suggesting that low-frequency stimulation to the right prefrontal cortex was possibly more effective. A single-blind randomized sham-controlled trial for 54 patients with antidepressant-nonresponding bipolar depression was performed (10). They concluded that 1-Hz 110% motor threshold and 300 pulses rTMS to the right prefrontal was not effective for bipolar depression over sham control. This failure was possibly attributed to a stimulus parameter (300 pulses/session for 15 sessions, with a total of 4,500 stimulation). Kito et al. conducted a preliminary study in which low-frequency stimulation was applied to the right prefrontal cortex and reported that the treatment was effective (11), safer, and more tolerable than high-frequency stimulation, a standard method of stimulation, applied to the left prefrontal cortex (11). The addition of 1-Hz 120% motor threshold and duration of 1,800 s (1,800 pulses) to the right prefrontal cortex rTMS to the usual medication will provide superior improvement of depressive symptoms compared to medication as usual for bipolar depression. However, a medium or large sample randomized, double-blind, sham-controlled study in this parameter has not yet been conducted. Therefore, as a therapeutic option for bipolar depression, we designed a medium sample, double blind, randomized, sham-controlled trial of low frequency (1,800 pulses/session for 20 sessions, with a total of 36,000 stimulation) to the right prefrontal cortex. This study aims to examine the efficacy and safety of 1-Hz rTMS to the right prefrontal cortex of patients with treatment-resistant bipolar depression. rTMS for bipolar depression was approved by the Ministry of Health, Labor, and Welfare as a highly advanced medical technology on March 1, 2019.

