### Intervention

#### Information on the medical devices

Based on a preceding study by McDonald (15), the conditions of stimulation by the Mag Pro R30 TMS device (Magventure) will be a frequency of 1 Hz, intensity of 120% motor threshold, and duration of 1,800 s (1,800 pulses) to the right prefrontal cortex, defined by the Beam F3 Location System (16), 5 days a week for 4 weeks during the acute treatment period, followed by a 3-week gradual reduction period (**Figure 2**). rTMS in a 3-week gradual reduction period will gradually reduce to 3 days a week in the first week, 2 days a week in the second week, and 1 day a week in the third week. Beam et al. have developed to find the F3 position using three skull measurement systems. The measurement of F4 (right DLPFC) is defined by Beam et al. (16) as follows:

Measurement of the distance from tragus to tragus and marking of the midpointMeasurement of the distance from nasion to inion (the midpoint is marked here as well, and the vertex is the point where the two lines containing the midpoints meet)Measurement of head circumference: Once these three measurements are attained, they are entered into the software package which provides two output values (values X and Y).A point along the circumference is marked X cm from the midline.F3 is marked as a point along the line running from the vertex through the point created in the previous step Y cm from the vertex.The “x” at the top of the head is the vertex; the other “x” is the F3 location.The opposite side of F3 from the midline is F4.

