**Figure 2 f2:**
[figure not shown]
Schedule of informed consent, baseline, acute treatment period, gradual reduction period, observation period.

The stimulation coil Cool-B65 A/P (Magventure) will be used. This coil was developed for use in clinical studies, and its internal system allows for assignment to the active or sham stimulation group under double-blind conditions. Assignment to the active or sham stimulation will be determined by the six-digit patient code that will be assigned to each patient in advance. In the active and sham stimulation groups, a stimulating electrode will be placed on the participant’s scalp to deliver weak sensory stimulation in synchronization with pulses; thus, the participants will not be able to differentiate between sham or active stimulation. In sham stimulation, although the same sensory stimulation will be administered as in actual stimulation, the intensity will not be enough to reach the brain. This system will ensure a blinded process for participants receiving sham stimulation in the control group. Both participants and staff will be unable to determine whether the stimulation is active or sham.

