### Evaluation of adverse events

Safety parameters are evaluated for each rTMS stimulation. Information relating to the adverse event, date of onset, date of resolution, severity, treatment, outcome, seriousness, and relationship to rTMS will be described in the medical record and case report form. When the relationship to rTMS cannot be ruled out, follow-up observations will be performed as much as possible until recovery to normal conditions. The terms used to describe adverse events conform to those provided by the Medical Dictionary for Regulatory Activities/Japanese version (MedDRA/J): International Conference on Harmonization (ICH).

The safety evaluation parameters are as follows:

Adverse events, particularly headache, stimulation site pain, stimulation site discomfort, presence or absence of muscle contraction (evaluated each time rTMS is delivered).The presence or absence of suicidal ideation (a parameter related to suicide in HAMD-17) and YMRS score (evaluated each time during the acute treatment and observation periods).

The results of the safety evaluation parameters should be recorded on the case report each time they are evaluated.

The severity of each adverse event is defined as follows:

Mild: the condition in which the participant feels discomfort but does not interfere with daily life.Moderate: the condition that restricts the participant’s daily life and makes the participant feel uncomfortable.Severe: the condition wherein the participant is unable to work or perform daily activities.

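### Adverse events are compared over the acute and observation periods only, the start of observation is inconsistent, and no planned comparison covers the full 26-session stimulation course

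*Protocol article*

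**What the plan says.** All references are to the protocol article.

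- **Adverse events.** Counts and proportions by arm "will be calculated during the acute treatment period and in the subsequent observation period, respectively", with a chi-square or Fisher test between arms. These are the only two windows named.
- **Intervention, Information on the medical devices.** Stimulation is given "5 days a week for 4 weeks during the acute treatment period, followed by a 3-week gradual reduction period". In those three further weeks it is delivered "3 days a week in the first week, 2 days a week in the second week, and 1 day a week in the third week".
- **Figure 2 caption.** "Schedule of informed consent, baseline, acute treatment period, gradual reduction period, observation period". The reduction period is an item of its own, between acute treatment and observation.
- **Evaluation of adverse events.** The section opens with "Safety parameters are evaluated for each rTMS stimulation". For the HAMD-17 suicide item and mania rating it then says "YMRS score (evaluated each time during the acute treatment and observation periods", again without the reduction period. The Evaluation section asks for both ratings at every rTMS delivery.
- **Outcomes, Secondary endpoints.** Time to relapse or recurrence in the observation period has its origin at the end of acute treatment.
- **Definition of case classification.** The same interval is counted from day one of the observation period.
- **Analytical method, Secondary endpoints.** The same interval is counted from a week 0 attached to the observation period. Elsewhere, week 0 is the start of rTMS.

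**The concern.** Safety is a stated objective alongside efficacy, and the Introduction describes a population at high risk of suicide attempt and manic switch. The events singled out for attention (headache, site pain or discomfort, muscle contraction) are tied to stimulation. The exposure of interest is therefore the whole stimulation course, which does not end with the acute period.

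The planned acute-period table stops at session 20. Whether sessions 21 to 26 are analysed at all depends on where the observation period begins, and the article gives two incompatible indications. If observation begins after the reduction weeks, their events are recorded but not compared. If it begins before them, those events are merged with a much longer stretch without stimulation. In neither case can a reader learn how many patients in each arm had an event while receiving the full course.

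**Working it through.** **1. The plan's own figure.** The Introduction gives "1,800 pulses/session for 20 sessions, with a total of 36,000 stimulation".

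- Acute sessions: 5 per week × 4 weeks = 20.
- Pulses: 20 × 1,800 = 36,000.

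This reproduces exactly, so the stated total describes the acute course alone.

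**2. The reduction period.** Inputs are from Information on the medical devices.

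- Sessions: 3 + 2 + 1 = 6.
- Full course: 20 + 6 = 26 sessions.
- Share in the reduction period: 6/26 = 23.1% of sessions.
- Share of the weeks on stimulation: 3/(4 + 3) = 3/7 = 42.9%.
- Pulses: 6 × 1,800 = 10,800 of 26 × 1,800 = 46,800, assuming that the pulse count per session does not change.

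These counts are for a patient who completes the schedule.

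**3. Where observation begins.**

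| Source | Implied start of observation |
|---|---|
| Figure 2 caption; Information on the medical devices | After the reduction period (end of week 7) |
| Outcomes, Secondary endpoints, with Definition of case classification | End of acute treatment (end of week 4) |

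The second row is an inference. One section puts the origin of the relapse clock at the end of acute treatment and the other puts it at the start of observation. If both describe the same clock, the two days coincide. If they do not coincide, the endpoint has two origins three weeks apart, and the boundary is still unsettled.

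Follow-up length does not decide it. With 30.44 days per month:

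- 28 weeks from the start of rTMS: 28 × 7/30.44 = 6.4 months.
- 4 + 28 = 32 weeks: 7.4 months.
- 4 + 3 + 28 = 35 weeks: 8.0 months.

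The first is closest to the stated 6 months, but it does not show which period the reduction weeks belong to.

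**4. Consequence under each reading.**

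- *Observation starts after the reduction period.* Sessions 21 to 26 lie in neither window.
- *Observation starts at the end of acute treatment.* Three weeks on stimulation are pooled with 28 − 7 = 21 stimulation-free weeks if week 28 is counted from the start of rTMS, or with 28 − 3 = 25 if it is counted from the end of acute treatment. The stimulated part is then 3/24 = 12.5% or 3/28 = 10.7% of the window.

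Under the second reading the two tables cannot be combined to recover the course-level proportion. A patient may have events in both windows, so the proportions do not add. The observation-period count also includes events that arose after the last stimulation.

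**The case against.** The strongest reply is that observation simply follows acute treatment. The two relapse-clock definitions together say so, and the Adverse events section speaks of the subsequent observation period directly after the acute one. On that reading every event is counted, the period wording for the suicide item and YMRS covers every session, and the apparent conflict with the Evaluation section disappears. Figures 2 and 3 might confirm it. This part of the objection stands. A reader might infer that reduction-period events are lost to the safety analysis, but the documents support that only as one of two readings.

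A reader might also infer that the safety result would be wrong either way. That goes too far. An acute-period proportion correctly describes the acute period, and an observation window that includes the reduction weeks still compares randomised groups. Nor can the effect be expressed as a shortfall in incidence. The article gives no per-session event risk, so any such figure would rest on an assumed risk held constant over sessions.

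It can further be said that table layout is usually left to the full protocol or the SAP, and that serious examples are picked up elsewhere. Convulsive seizure, worsening suicidal ideation and a raised YMRS are discontinuation criteria, and suicidal ideation and manic switch are secondary endpoints. The second point stands for data capture. It does not supply a comparison over the reduction weeks, because the planned between-arm YMRS comparisons are at weeks 4 and 28. On the first point, the article does not leave the windows open. It fixes two of them, using a period name whose start it defines inconsistently.

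**Conclusion.** The point holds as a defect in the safety analysis windows. Adverse events are compared in two periods, while stimulation runs through a third that the schedule lists separately and that holds 6 of 26 sessions (23%) and 3 of 7 weeks on stimulation (43%). The start of observation is inconsistent. Depending on how it is resolved, events at sessions 21 to 26 are either in no window or mixed with 21 to 25 stimulation-free weeks. Under both readings the plan has no comparison over the full course.

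It is not established that these events are excluded or that they go uncollected. Safety data are required at each stimulation. No test of the primary endpoint and no sample-size figure is affected. The counts assume that a patient completes the schedule. Confidence is moderate, because the schedule figures could not be seen and may fix the boundary. The change is still worth making, since an on-stimulation comparison is absent on either reading.

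**What to change.** 1. State once on which day the observation period begins. Use that day in Evaluation of adverse events, Outcomes (Secondary endpoints), Definition of case classification, Analytical method (Secondary endpoints) and Adverse events.
2. In Adverse events, add a between-arm comparison over the on-stimulation period, from first to last stimulation (acute plus gradual reduction), and a separate one over stimulation-free follow-up. Keep the acute-period table.
3. Reconcile the period wording for the suicide item and YMRS in Evaluation of adverse events with the Evaluation section, which requires them at every delivery. The sponsor should say which schedule was intended.

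The cost is a few sentences and some extra table columns. No new data are needed if ratings are taken at each session as the Evaluation section requires. Recruitment is expected to run to February 2027 and unblinding follows data fixation, so the windows can be settled before any comparative result is known.

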### Criteria for discontinuation of individual study participant

If the principal investigator, principal investigator, or sub-principal investigator determines that it is not feasible to continue research on an individual research subject for any of the following reasons, the research on that research subject will be terminated. With full consideration given to the ethical aspects of study subjects, information on observations and tests related to the primary and secondary endpoints will be collected after the point of discontinuation to the greatest extent possible.

Withdrawal of consent or request for withdrawal to participate by the study participants.It is revealed after enrollment that the eligibility criteria were not met.Suicidal ideation is exacerbated (HAMD-17 score for suicide, ≥3) and continuation of the study is considered unfavorable.The total YMRS score is ≥8.The occurrence of an adverse event makes it difficult to continue the study.Pregnancy.Significantly poor compliance (rTMS is performed 2 days or less in 2 consecutive weeks).Occurrence of a convulsive seizure.Relapse/recurrence during the observation period.Discontinuation of the entire study, andThe investigator considers it appropriate to discontinue the study for other reasons.

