### Statistical analysis

Statistical analysis will be conducted using the Statistical Analysis System software. All statistical tests will be two-sided, and the significance level will be set at 0.05. The primary analysis set of the efficacy and safety is the full analysis set (FAS), which will consist of all the randomized patients except those in whom neither active nor sham stimulation was performed. The secondary analysis set is the per protocol set (PPS), which will consist of all the eligible cases defined below.

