### Definition of case classification

Eligible cases: the participants who meet all the inclusion criteria and do not meet any of the exclusion criteria.

Discontinued cases: the participants who discontinued the study according to the criteria of discontinuation of individual case.

Handling the data of discontinued cases or missing values:

Discontinued casesFor the FAS, the values measured until the discontinuation time will be used for evaluation irrespective of the discontinuation time. For the PPS, the discontinued cases will be treated as missing values if the participant discontinues the study <4 weeks from the start of the study. Measured values will be used if the participant discontinues the study >4 weeks after the start of the study.Missing valuesThe primary endpoint, the MADRS total score, will be analyzed using mixed-effects models for repeated measures (MMRM) including those patients who had some missing values. Moreover, sensitivity analyses will be performed using single imputation methods such as baseline observation carried forward (BOCF) that performs an evaluation by substituting values measured at baseline for missing values and last observation carried forward (LOCF) by substituting the last measured value prior to the missing values. As for multiple imputation, distributions are assumed for the missing values with different parameters of the distribution according to conditions such as treatment methods. Additionally, a supplementary complete case analysis will be performed with participants having no missing data during the period of acute phase treatment.The time (days) to relapse or recurrence during the observation period, a secondary endpoint, will be defined as the interval (days) from the first day of the observation period to the date when the relapse or recurrence was identified. If a patient had not come to hospital before week 28 of the observation period, two types of handling of data will be considered; one is that the relapse or recurrence date will be regarded as 7 days after the final evaluation date, and the other is that the observation will be treated as censored on the final evaluation date. If no relapse or recurrence is confirmed at 28 weeks, the observation will be treated as censored on the day of 28 weeks.

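### Observation-period adverse events are compared as crude proportions with no account of follow-up time, so unequal stopping between arms can distort the comparison in either direction

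*Protocol article*

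**What the plan says.** Four parts of the protocol article bear on this.

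- **Adverse events:** for each arm, counts and proportions with events "will be calculated during the acute treatment period and in the subsequent observation period, respectively". On testing, the section adds: "Both groups will be compared and analyzed using chi-square test or Fisher test". It names no denominator for the observation period and no measure of follow-up.
- **Statistical analysis:** "The primary analysis set of the efficacy and safety is the full analysis set (FAS". This set is all randomized patients who received at least some active or sham stimulation. No other primary safety set is named.
- **Criteria for discontinuation of individual study participant:** the reasons include "Relapse/recurrence during the observation period", "The total YMRS score is ≥8", worsened suicidal ideation, an adverse event that makes continuation difficult, and a seizure. The same section says that information on the primary and secondary endpoints "will be collected after the point of discontinuation to the greatest extent possible".
- **Definition of case classification:** for the FAS, "the values measured until the discontinuation time will be used for evaluation irrespective of the discontinuation time".

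Adverse events, suicidal ideation and manic switch are listed among the secondary endpoints, and safety is part of the stated objective.

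**The concern.** The observation period runs to week 28, so it lasts months. A patient stopped in week 2 of it has had far less opportunity to report an event than one who completes it, yet a crude proportion treats both as fully observed. Several stopping reasons are outcomes that treatment may influence. Relapse is one: it is defined only after remission, so a treatment that produces more remissions also changes how many patients can be stopped for relapse. Unequal time at risk is therefore plausible.

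Elsewhere the protocol does deal with incomplete follow-up. Time to relapse or recurrence over the same period is analysed with censoring, Kaplan–Meier and a log-rank test. Adverse events get no comparable treatment. At stake are the reported safety proportions and their difference, which readers will use to judge tolerability after the acute phase.

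**Working it through.** **Inputs from the document.** There are 38 analysed patients per arm. This figure reproduces: 2 × (1.960 + 0.842)² / 0.65² = 37.2, rounded up to 38; and 38 / 0.80 = 47.5, rounded up to 48 consented. The document gives no adverse event rate and no stopping rate, so every rate below is an assumption.

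**Check 1: same true risk p in both arms, constant hazard, stops spread evenly over the period.** Let s be the share of entrants who stop during observation. A patient who stops has an average chance of an event before stopping of 1 − p / (−ln(1 − p)). The length of the period cancels out.

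- p = 30%: 1 − 0.30/0.3567 = 0.1589
- p = 50%: 1 − 0.50/0.6931 = 0.2787

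Observed proportion among entrants = (1 − s) × p + s × that value:

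| True risk | s = 20% | s = 40% | False difference |
|---|---|---|---|
| 30% | 0.8 × 0.30 + 0.2 × 0.1589 = 27.2% | 0.6 × 0.30 + 0.4 × 0.1589 = 24.4% | 2.8 points |
| 50% | 0.8 × 0.50 + 0.2 × 0.2787 = 45.6% | 0.6 × 0.50 + 0.4 × 0.2787 = 41.1% | 4.4 points |

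This part arises with everyone entering, so it does not depend on which denominator is meant.

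Now let 20% of active and 5% of sham patients never enter, with s = 20% in both arms and the whole FAS as denominator:

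- p = 30%: 0.80 × 27.2% = 21.7% v 0.95 × 27.2% = 25.8%, a false 4.1 points
- p = 50%: 0.80 × 45.6% = 36.5% v 0.95 × 45.6% = 43.3%, a false 6.8 points

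With entrants as denominator, both arms show 27.2% (or 45.6%) and this difference disappears.

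**Check 2: both mechanisms together, exponential stopping, 24 weeks assumed (week 4 to week 28), first events counted.** True risk is 30% in both arms; one arm has 5% non-entry and 20% stopping, the other 15% and 40%. The chance that an entrant has an event before stopping is λ/(λ + μ) × (1 − e^(−(λ+μ)T)), with λT = −ln 0.70 = 0.357 and μT = −ln 0.80 = 0.223 or −ln 0.60 = 0.511.

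- Entrants: 0.357/0.580 × (1 − 0.56) = 27.1% v 0.357/0.868 × (1 − 0.42) = 23.8%
- FAS: 0.95 × 27.1% = 25.7% v 0.85 × 23.8% = 20.3%
- Events per patient-week: 0.357/24 = 0.0149 in both arms

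The rate recovers the equal hazards; an entrants denominator removes only part of the gap.

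**Check 3: direction.** In Check 2, suppose the stops during observation are themselves counted as adverse events. If all are, the FAS proportions become 0.95 × (1 − 0.56) = 41.8% v 0.85 × (1 − 0.42) = 49.3%. If half are, they are 33.8% v 34.8%. The arm that stops more no longer looks safer. That excess is partly real, since the arm then has more counted events.

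**Scale.** With 38 per arm, 2.8 to 4.4 points is 1.1 to 1.7 patients, and 4.1 to 6.8 points is 1.6 to 2.6 patients. Across the scenarios tried (true risk 20% to 50%, non-entry 5% to 20%, stopping 10% to 60%), the approximate chance of a significant result ran from 3% to 29%. The top value came from the most extreme pattern, 5% v 20% non-entry with 20% v 60% stopping.

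**The case against.** The strongest reply is that this is an ordinary descriptive safety table in a condensed article, and that table denominators usually sit in an analysis plan that is not shown. That stands for the denominator. A reader might infer that non-entrants are certainly counted as event-free, because the FAS is the only primary safety set named. The Adverse events section does not say so, and a table of FAS patients at risk in the period would be compatible with the text. The 4 to 7 points depend on that inference. The reply does not remove the point, because the summary measure and tests are stated and ignore follow-up under either denominator.

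A reader might also infer that the arm that stops more will simply look safer. The documents do not support that as a general statement: seizure, adverse events, suicidal ideation and mania scores are stopping reasons that may themselves be counted, and Check 3 shows the sign can change.

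Nor does follow-up necessarily end at discontinuation, since endpoint information is to be collected afterwards as far as possible. If those data were used, the distortion would shrink. But the handling of discontinued cases uses FAS values only until discontinuation, and whether that rule reaches adverse events is unclear.

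Finally, the events singled out (headache, pain and discomfort at the stimulation site, muscle contraction) are tied to stimulation, so the acute-period table carries the main safety comparison. That stands, and nothing here calls for a change to the acute-period analysis.

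**Conclusion.** The point holds in a conditional form. The stated observation-period comparison ignores time at risk, although the protocol's own stopping rules can make time at risk depend on outcome and on arm. If stopping is equal between arms there is no between-arm distortion, although both proportions understate the full-period risk. If it is unequal, the assumed scenarios give a false difference of about 3 to 4 points from stopping during observation, and about 4 to 7 points from non-entry only under a whole-FAS denominator. Neither size nor direction can be fixed from the documents, because they give no stopping or adverse event rates. The effect is on the reported proportions and their difference more than on significance. It does not touch the primary endpoint.

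**What to change.** In the Adverse events section, keep the planned proportions and tests. For the observation period, add events per patient-week of observed follow-up by arm, with a rate difference or ratio and 95% CI. Alternatively, use time to first event with censoring, as already planned for relapse. Show the number of FAS patients who enter the period beside the proportions, and name the denominator used. An entrants-only denominator should not be the whole remedy: it conditions on something that happens after randomization and leaves unequal follow-up in place.

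Reconcile the collection of endpoint information after discontinuation with the use of FAS values only until discontinuation, so that it is clear whether adverse events after stopping count. Patient-weeks should then be counted over the same window as the events.

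The cost is some wording and one extra table. Onset dates are recorded for each adverse event, and the relapse analysis already relies on final evaluation dates. Recruitment is still open and unblinding follows data fixation, so the change can be made blind. Two limits remain: the rate assumes a roughly constant hazard, and neither it nor censoring fully removes the effect of stopping that is related to outcome.
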